**Methods and analysis:**

This prospective cohort study will investigate the effectiveness of care delivery at the AGCH on patient outcomes by comparing AGCH patients to two historic cohorts of hospitalised patients. Propensity score matching will correct for potential population differences. The primary outcome is the 3-month unplanned readmission rate. Secondary outcomes include functional decline, institutionalisation, healthcare utilisation, occurrence of delirium or falls, health-related quality of life, mortality and patient satisfaction. Measurements will be conducted at admission, discharge and 1, 3 and 6 months after discharge. Furthermore, an economic evaluation and qualitative process evaluation to assess facilitators and barriers to implementation are planned.

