### Outcomes

The primary outcome measure is the 3-month unplanned readmission rate to the AGCH or hospital.

Secondary outcomes measured at 1, 3 and 6 months will include:

Activities of Daily Living (ADL)-functioning, as defined by the Katz-ADL scale.^36^Healthcare utilisation, including institutionalisation in a long-term care facility.Occurrence of delirium and/or falls.HRQOL.^37^All-cause mortality.Satisfaction of the patients and primary caregivers with the provided care.

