### Sample size calculation

In the Hospital-ADL study, 34% of participants experienced a readmission at 90 days.^35^ Assuming that 26% of patients admitted to the AGCH will experience a 90-day readmission, data from 515 patients at the AGCH will yield 80% power to detect an absolute difference of 8% in the readmission rate (which is a 25% reduction in the relative risk) using a two-sided test with an alpha of 0.05.^55^ As we expect 10% loss to follow-up, we aim to include a total of 567 (=515*1.10) patients from the AGCH.

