### Planned statistical analyses

The complete participant flow diagram will show a summary of admissions and study recruitment at the AGCH and will provide study discontinuation rates at 1, 3 and 6-months follow-up.^30^ We will describe the demographic, clinical and prognostic characteristics of the study participants at baseline. The number of participants with missing data will be collected and described alongside our variables to check for the pattern of missingness. Inversely weighted propensity scores will be used to control for any imbalances between the treatment groups.^56^ Propensity scores will be calculated using generalised booted methods. Balance and overlap of propensity score distribution will be assessed. Propensity score weights for the estimation of the average treatment effect will be created using all covariates where groups differed at baseline or that were associated with the 90-day readmission rate. As this is a repeated measures design, we will assume equal weighting for all measurements.^57^

All hypotheses will be tested using a two-tailed significance level of 0.05. All secondary outcomes will be adjusted for multiple testing using a Hochberg method.^58 59^ Descriptive analyses will be performed to examine the participants’ characteristics. Differences in changes over time in outcomes will be compared between groups using multilevel models. All models will include a main effect of treatment group, a linear term for time and an interaction between time and treatment group. Models will be checked with residual and appropriate goodness-of-fit statistics.

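### The Hochberg family includes mortality, falls and delirium, so an excess of any of these with a raw p between 0.05/m and 0.05 can be labelled non-significant

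*Protocol article*

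**What the plan says.** Under Planned statistical analyses the protocol article fixes the level, "All hypotheses will be tested using a two-tailed significance level of 0.05", and the multiplicity rule, "All secondary outcomes will be adjusted for multiple testing using a Hochberg method". No outcome is exempted.

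The Outcomes section introduces its list with "Secondary outcomes measured at 1, 3 and 6 months will include". The list has six items: ADL functioning, healthcare utilisation with institutionalisation, "Occurrence of delirium and/or falls", quality of life, "All-cause mortality", and satisfaction. The abstract gives the same group: "Secondary outcomes include functional decline, institutionalisation, healthcare utilisation, occurrence of delirium or falls, health-related quality of life, mortality and patient satisfaction". Mortality, falls and delirium are therefore inside the adjusted family.

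The primary outcome, unplanned readmission at three months, is outside it. The number of tests in the family is not given.

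**The concern.** Adjusting for multiplicity protects against false claims of benefit, and the hypothesis in the Introduction is one of benefit. For harm the more costly error is to miss it, and a single adjusted family raises the threshold for seeing it. The threshold also depends on outcomes that have nothing to do with safety: adding satisfaction to the family makes an excess of deaths harder to call significant.

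This matters here because, as the Setting section describes, the AGCH treats acutely ill older patients at a site with laboratory testing on working days and simple X-ray once a week. The article also says the findings are meant to support financing and implementation elsewhere. Whether patients fare worse on mortality, falls or delirium is part of what those decisions will rest on.

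**Working it through.** **Inputs from the article.** Two-sided alpha of 0.05 and Hochberg for all secondary outcomes (Planned statistical analyses). Six listed outcomes (Outcomes). 515 AGCH patients with data (Sample size calculation). Control cohorts of 401 and 674, together 1,075 (Historical control groups).

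**Assumptions.** m = 6, one test per listed item; splitting delirium from falls, or institutionalisation from utilisation, gives 7 or 8. Mortality of 15% in controls and 20% at the AGCH. No loss of precision from propensity weighting, so the power figures are optimistic.

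**The plan's own figure.** "In the Hospital-ADL study, 34% of participants experienced a readmission at 90 days", and 26% is assumed at the AGCH. With pooled variance under the null and equal groups, n = [1.960 × √(2 × 0.30 × 0.70) + 0.842 × √(0.34 × 0.66 + 0.26 × 0.74)]² / 0.08² = 513.9, so 514 against the stated 515. The sample size reproduces and nothing in it is at issue.

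**The Hochberg rule.** Order the p-values p(1) ≤ … ≤ p(m). Find the largest k with p(k) ≤ 0.05/(m − k + 1) and reject hypotheses 1 to k. If the harm is the only signal it must meet 0.05/m:

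- m = 6: 0.0083
- m = 7: 0.0071
- m = 8: 0.0063

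With m = 6, a raw p of 0.02 for excess deaths becomes up to 6 × 0.02 = 0.12.

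**Loss of power whatever the event rates.** A harm with 80% power at 0.05 has an expected z of 1.960 + 0.842 = 2.802. The critical value at 0.05/6, two-sided, is 2.638. Power is Φ(2.802 − 2.638) = Φ(0.163) = 56.5%. For m = 7 and m = 8 it is 54% and 53%. A simulation of the full step-up procedure with m = 6 gave 56.6% with all other outcomes null, and 62–63% when three of the other five carried a true benefit with 80% power each. The 56.5% is thus the bottom of the range for six tests.

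**Illustration with the assumed mortality rates.** Power = Φ(0.05/SE − critical value), with SE = √(0.20 × 0.80/515 + 0.15 × 0.85/n).

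| Controls | SE | 0.05/SE | Power at 0.05 | Power at 0.05/6 |
|---|---|---|---|---|
| 401 | 0.02507 | 1.994 | 51.4% | 26.0% |
| 1,075 | 0.02072 | 2.413 | 67.5% | 41.1% |

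With pooled variance under the null the figures are 50% and 25% for 401 controls, and 70% and 45% for 1,075. The choice of formula does not change the picture.

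**When the outcomes are measured.** The Outcomes section refers to 1, 3 and 6 months. Table 1 schedules delirium at admission and discharge only, satisfaction at discharge (or at one month if missed), and mortality and falls through to six months. Any report of these outcomes should follow Table 1.

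**The case against.** The best case for the plan is that one adjusted family for all pre-specified secondary outcomes is coherent and symmetric. Every outcome can move either way, and the article lists mortality, falls and delirium as effectiveness outcomes. Adjusting p-values changes neither the estimates nor unadjusted confidence intervals, so a harm stays visible if those are shown. Even unadjusted, power for the assumed mortality excess is only 51% to 67.5%, so a non-significant result would say little in any case. A rule that adjusts only when the direction is favourable would also sit awkwardly with two-sided testing.

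Much of this stands, and it rules out several stronger readings that a reader might infer:

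- **That these are the study's only harm outcomes.** They are not. Unplanned readmission is primary and tested outside the family, and ADL decline and institutionalisation can also worsen.
- **That six outcomes at three visits make 18 tests.** The plan compares changes over time in multilevel models with a group-by-time interaction, and Table 1 does not schedule delirium or satisfaction at all three visits.
- **That a harm will be hidden.** 0.05/m is the worst case, and if every secondary p-value is at most 0.05 nothing is lost.
- **That no safety reporting is planned, or that adjusted non-significance will be taken as safety.** A condensed article cannot show the first, and it does not say the second.

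What the objection does not remove is the stated rule itself. It covers all secondary outcomes, and these three are among them. The point about direction is met if the unadjusted interval is shown whichever way the result falls, with Hochberg deciding only whether a benefit may be claimed.

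**Conclusion.** The concern holds in a limited form. As written, the rule lets an excess of deaths, falls or delirium with a raw p between 0.05/m and 0.05 be labelled non-significant. With about six tests the worst-case threshold is 0.0083, and power of 80% falls to about 57%. The mortality illustration (51% to 26%, or 67.5% to 41%) rests on assumed rates, on m = 6, on no other secondary outcome being significant, and on no loss from weighting. No stated figure is wrong, no passages conflict on the rule, and the primary analysis is untouched. It is a minor weakness with a cheap remedy.

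**What to change.** In Planned statistical analyses, limit Hochberg to claims of benefit on secondary outcomes. Add that mortality, falls and delirium will also be reported as safety outcomes, each with the propensity-weighted difference and a 95% confidence interval not adjusted for multiplicity, at the times Table 1 measures it. State that an adjusted non-significant result will not be read as absence of harm.

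This costs one or two sentences and needs no new data. The downside is a somewhat higher chance of a false alarm. With no true difference, each interval lies wholly on the harm side 2.5% of the time, so for three outcomes at one time point each the chance of at least one is at most 3 × 2.5% = 7.5%. Delirium needs particular care: the Hospital-ADL cohort excluded delirious patients, so a higher rate at the AGCH could reflect selection, and the report should say so beside the estimate.

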The AGCH delivers acute care that is focused on early mobilisation and rehabilitation. Older persons with common medical problems (such as urinary tract infections, pneumonia or heart failure) and geriatric syndromes requiring hospital admission can be admitted to the AGCH. The AGCH provides a form of *intermediate* care between primary and secondary care. In the Netherlands, primary care includes general practice, community nursing and (temporary) admission to a nursing home. Secondary care includes specialist medical care and hospital admission. The care at the AGCH is supervised by a geriatrician and provided by nurses trained in geriatric care who have experience as either a hospital or community nurse. The single rooms are designed to accommodate respite for the informal caregivers. This concept of care is new to the Netherlands, and to our knowledge, there is only one comparable example in Europe: a ‘subacute care unit’ in intermediate care, which has been implemented in Spain.^27^

Our hypothesis is that with the provision of integrated medical and nursing care close to home, the AGCH is better suited to the needs of older adults with multiple chronic conditions and will lead to better patient health outcomes and reduced post-acute care costs. Therefore, this study is designed to compare care provided for older patients in the AGCH versus care provided in a hospital setting. Specifically, we aim to:

Evaluate the 90-day readmission rate of patients acutely admitted to the AGCH compared with a traditional hospital (usual care). Secondary outcomes include functional decline, institutionalisation, healthcare utilisation, the occurrence of geriatric syndromes such as delirium, health-related quality of life (HRQOL), mortality and patient satisfaction;Assess the cost-effectiveness of the AGCH versus usual care by performing an economic evaluation from a healthcare provider and societal perspective;Conduct a process evaluation using interviews with key stakeholders to identify facilitators and barriers to the implementation of the AGCH.

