##### Functioning level

The 15-item modified Katz-ADL score is used to measure ADL functioning. This includes statements about independence in performing basic ADL and in instrumental ADL (IADL).^46 47^ We measure the Katz-ADL both currently (at admission), as well as 2 weeks before admission, reflecting pre-morbid level of functioning. The Katz-ADL is also measured during follow-up.

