**Figure 2 F2:**
[figure not shown]
Diagram of patient participation between February 1st and December 20th, 2019.

**Table 2 T2:** Baseline characteristics of the study participants

Variable	N=212
Age in years, mean (SD)	81.8 (8.4)
Male, N (%)	101 (47.6)
Living arrangements before admission, N (%)	
Independent	172 (81.1)
Assisted living/senior residence	31 (14.6)
Nursing home/other	9 (4.2)
Marital status, N (%)	
Widow/widower	94 (44.5)
Married or living together	71 (33.6)
Single or divorced	46 (21.8)
Education, N (%)	
Primary school	36 (18.7)
Elementary technical/domestic science school	41 (21.2)
Secondary vocational education	65 (33.7)
Higher level high school/third-level education	51 (26.4)
Born in the Netherlands, N (%)	158 (76.0)
Katz-ADL (6-item) score* upon admission, median (IQR)	3.0 (1.0-5.0)
MMSE score†, mean (SD)	23.7 (4.7)
Polypharmacy‡, N (%)	159 (75.0)
Hospitalisation in past 6 months, N (%)	61 (31.1)
Charlson Comorbidity Index§, mean (SD)	2.8 (2.0)
Primary admission diagnosis, N (%)	
Infectious diseases	60 (28.3)
Respiratory (including pneumonia)	54 (25.5)
Gastrointestinal	9 (4.2)
Cardiovascular	20 (9.4)
Neurological	16 (7.5)
Other (eg, falls, delirium, sudden unexplained functional decline)	53 (25.1)

*Score ranging from 0 to 6, with a higher score indicating more dependence in activities of daily living.^36^

†Score ranging from 0 to 30, with a score of ≤23 indicating possible cognitive impairment.^31^

‡Use of five drugs or more.

§Ranging from 0 to 31, with a higher score indicating more severe comorbidity.^39^

ADL, activities of daily living; MMSE, Mini-Mental State Examination.

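### The stated Katz-ADL model ties functional decline to neither of the two baseline scores collected, so it may mix recovery with decline or capture only post-discharge drift

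*Protocol article*

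**What the plan says.** The aims at the end of the Background section state: "Secondary outcomes include functional decline, institutionalisation, healthcare utilisation". The Outcomes section turns this into "Activities of Daily Living (ADL)-functioning, as defined by the Katz-ADL scale" under the lead-in "Secondary outcomes measured at 1, 3 and 6 months will include". It gives no reference value.

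The Functioning level section describes two entry values: "We measure the Katz-ADL both currently (at admission), as well as 2 weeks before admission, reflecting pre-morbid level of functioning". It adds: "The Katz-ADL is also measured during follow-up".

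Planned statistical analyses gives one approach for all outcomes: "Differences in changes over time in outcomes will be compared between groups using multilevel models". The terms are then listed: "All models will include a main effect of treatment group, a linear term for time and an interaction between time and treatment group". The same section describes propensity weights built from covariates that differ between groups at baseline or are associated with 90-day readmission. It names no Katz score among them.

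**The concern.** Decline needs a reference point, and for an acutely ill older patient the choice matters. Function often falls with the acute illness, and part of the loss may return whatever care is given. A patient who was independent, is admitted needing help with 4 of 6 items and ends needing help with 2 has improved by 2 since admission and declined by 2 from the pre-morbid level. The protocol collects the value that separates these two statements but does not give it a role in the stated model.

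The groups may also differ in acute loss. AGCH eligibility requires a geriatric condition such as delirium, falls or functional impairment in addition to the acute problem. In Table 2, 53 of 212 participants fall in the category "Other (eg, falls, delirium, sudden unexplained functional decline". The 401-patient Hospital-ADL control cohort excluded delirium and severe cognitive impairment. If acute loss differs and admission is part of the modelled series, unequal rebound could be read as an effect of the care setting.

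**Working it through.** No figure in the protocol bears directly on this point, so there is none to reproduce. The check takes the possible starting points of the time series in turn.

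**Inputs**
- From Table 2: AGCH admission Katz median 3.0 (IQR 1.0–5.0) on the 6-item scale, 0 to 6, higher meaning more dependent. It is used below as if it were a mean.
- Assumed: the same pre-morbid score in both groups, a score of 2.0 in both groups at months 1, 3 and 6, a control admission mean between 1.0 and 3.0, and admission coded as month 0. With these values the true group difference in change from the pre-morbid level is 0.

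**Reading A: admission is an outcome occasion (t = 0, 1, 3, 6).**
The least-squares slope is Σ(t − t̄)y / Σ(t − t̄)².
- t̄ = 10/4 = 2.5.
- Σ(t − t̄)² = 6.25 + 2.25 + 0.25 + 12.25 = 21.
- Only the admission score differs, by D = AGCH minus control. The slope difference is therefore −2.5 × D / 21 = −0.119D per month, or 6 × (−2.5/21) × D = −0.714D over 6 months.

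| Control admission mean | D | Spurious difference over 6 months (Katz points) |
|---|---|---|
| 3.0 | 0 | 0 |
| 2.5 | 0.5 | −0.36 |
| 2.0 | 1.0 | −0.71 |
| 1.5 | 1.5 | −1.07 |
| 1.0 | 2.0 | −1.43 |

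A negative value looks like an AGCH benefit. If the control group had the higher admission score, the sign would reverse. D here is the difference that remains after weighting, not the raw difference.

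**Reading B: only months 1, 3 and 6 are modelled.**
The admission score drops out, and the slope difference is 0 in every row above. But suppose AGCH patients score better by a constant δ at all three visits. Its contribution to the slope is δ × Σ(t − t̄) / Σ(t − t̄)², and Σ(t − t̄) = 0, so the group-by-time term is 0. A full benefit that is present by month 1 and maintained is invisible to the comparison of changes. The group main effect would pick up δ as a difference in level. Without the pre-morbid score, though, that level does not show whether patients lost function.

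**Reading C: the pre-morbid score is the first occasion and admission the second.**
A single linear time term cannot describe a fall followed by partial recovery.

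**Weighting.** Balancing the admission score alone does not balance acute loss. Two patients admitted at 4 of 6, one previously at 0 and the other previously at 4, have lost 4 and 0 points and can be expected to rebound differently. Both scores are needed.

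**Comparison within the same article.** The Economic evaluation section adjusts the QALY model for baseline utility. The Katz model has no stated counterpart.

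**The case against.** The strongest reply is that the article does not commit to an acute-illness baseline. The sentence on changes over time is generic and names no starting point, and the Outcomes section lists only 1, 3 and 6 months. The list of model terms sets a minimum and does not exclude covariates. Which value anchors one secondary outcome may be settled in a full protocol or analysis plan that is not shown. All of this stands. A reader might infer that the plan measures decline from the admission trough in place of the pre-morbid score; the text does not say so.

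A reader might also infer that AGCH patients start from a deeper trough and that the bias favours the AGCH. The documents do not support a direction. They give no pre-morbid Katz, no control-cohort Katz and no recovery rate. The 53 of 212 patients mix falls, delirium and functional decline. The geriatric conditions required for entry can be long-standing, in which case a high admission score reflects chronic dependence. The delirium exclusion is stated for the 401-patient cohort only, while the 674-patient cohort included severe cognitive impairment with proxy consent.

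Weighting is a real safeguard: if either Katz score differs at baseline, the selection rule would bring it into the weights, and much of any difference could disappear. It is also true that, once the pre-morbid score is a linear covariate, analysing change from that score or the raw follow-up score gives the same treatment coefficient.

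What remains is that the article prescribes terms for all models, and on none of the three readings do those terms alone estimate decline from the pre-morbid level. The equivalence of change and raw score holds only once the covariate is in the model, which is the change requested.

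**Conclusion.** The point holds as a gap between a named outcome and its stated model. Two candidate baselines are collected, the outcome is called decline, and the prescribed comparison uses neither as reference or covariate.

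The size is conditional. With admission as an outcome occasion, each 1-point difference in admission score left after weighting produces about 0.7 Katz points of spurious difference over 6 months, given equal pre-morbid and follow-up scores. It is 0 if weighting equalises the admission score under those same assumptions, or if only the follow-up visits are modelled. In the latter case the loss is of a different kind: an early, sustained effect does not appear in the interaction.

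Neither the presence nor the direction of a bias is shown. This concerns one secondary outcome and leaves the primary readmission outcome untouched.

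**What to change.** Add to Planned statistical analyses wording such as: *For Katz-ADL, groups are compared on the scores at 1, 3 and 6 months. The score 2 weeks before admission and the score at admission are baseline covariates and enter the propensity model. Functional decline is expressed relative to the score 2 weeks before admission. The admission score is not an outcome occasion. Change from admission is reported separately as recovery.* The group contrast should be given at each visit, so that an effect already present at 1 month is seen.

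For the AGCH group this needs no new data. There are two downsides. The pre-morbid score is recalled or reported by proxy, so it carries error. Its availability in both historic cohorts must also be confirmed: the Data collection section says the measurements were chosen from those made in the control groups, but the supplementary comparison table is not shown here. If one cohort lacks the score, the protocol should say so and limit the decline analysis accordingly.

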##### Permanent institutionalisation

This concerns long-term admission to a skilled nursing facility and the date of admission to this facility.

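### Death and permanent institutionalisation are dated one-time events, but the only stated outcome analysis is a change-over-time model, whose natural test (a logit-scale group-by-time interaction) is nearly blind to a proportional excess of deaths

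*Protocol article*

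**What the plan says.** The Outcomes section opens its list with "Secondary outcomes measured at 1, 3 and 6 months will include". The list contains "All-cause mortality" and, under healthcare utilisation, institutionalisation in long-term care.

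Both events are dated. Table 1 records the date of death from the discharge assessment onwards. The section on permanent institutionalisation says "This concerns long-term admission to a skilled nursing facility and the date of admission to this facility".

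Planned statistical analyses gives one form of group comparison: "Differences in changes over time in outcomes will be compared between groups using multilevel models". It continues: "All models will include a main effect of treatment group, a linear term for time and an interaction between time and treatment group". The same section frames the data as repeated measurements: "As this is a repeated measures design, we will assume equal weighting for all measurements".

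The article names no time-to-event model, no competing-risk method and no separate rule for one-time events. It also does not name the link function or the coefficient to be tested.

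**The concern.** A multilevel model of change suits outcomes that can rise and fall within a patient, such as Katz-ADL or EQ-5D. Death cannot reverse. At the three follow-up visits the only possible sequences of death status are 000, 001, 011 and 111. Within-patient change then carries no information beyond when the event happened, and a patient random effect is close to degenerate.

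The contrast also matters. A treatment that multiplies the hazard of death by a constant shifts the log-odds of being dead by nearly the same amount at every visit. The groups then differ in level on that scale but hardly in slope, and a test of differing change looks at the slope.

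Mortality is a main harm outcome when acute care moves out of hospital, and the results are meant to support wider implementation and financing. A non-significant interaction could be read as reassurance on mortality when the test had little chance of showing otherwise.

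**Working it through.** **Inputs.** The AGCH sample of 515 comes from the Sample size calculation section. It rests on readmission: "In the Hospital-ADL study, 34% of participants experienced a readmission at 90 days", against 26% assumed for the AGCH. It reproduces: [1.96·√(2·0.30·0.70) + 0.8416·√(0.34·0.66 + 0.26·0.74)]² / 0.08² = (1.270 + 0.543)² / 0.0064 ≈ 514 per group, and 515 per group gives 80.1% power. The 401 controls are the Hospital-ADL cohort. On the error rate the article says "All hypotheses will be tested using a two-tailed significance level of 0.05". It gives no mortality figure, so 6-month mortality of 20% (control) and 28% (AGCH) with constant hazards is an assumption.

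**Shape of the effect.** The monthly hazard is h = −ln(1 − p₆)/6, which gives 0.0372 and 0.0548, a hazard ratio of 1.47. Risk at month t is 1 − exp(−h·t).

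| Month | Control | AGCH | Risk difference | Log odds ratio |
|---|---|---|---|---|
| 1 | 3.7% | 5.3% | 1.7 points | 0.40 |
| 3 | 10.6% | 15.2% | 4.6 points | 0.41 |
| 6 | 20.0% | 28.0% | 8.0 points | 0.44 |

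On the logit scale the gap moves by about 0.04 in five months, so there is almost no interaction to find. On the risk scale it widens by about (8.0 − 1.7)/5 ≈ 1.3 points per month, so an identity-link interaction can find it.

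**Hand checks of attainable power.**
- Log-rank (Schoenfeld): expected deaths 515·0.28 + 401·0.20 = 224.4; AGCH share 515/916 = 0.562; z = √(224.4·0.562·0.438)·ln(1.472) ≈ 2.87; power = Φ(2.87 − 1.96) ≈ 82%.
- Two proportions at 6 months: pooled standard error 0.0286, unpooled 0.0281; power = Φ[(0.08 − 1.96·0.0286)/0.0281] ≈ 80%.

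**Simulation of the stated terms.** Exponential death times, 515 vs 401, 20% vs 28%; marginal binary model with group, linear time and interaction, robust standard errors; no propensity weights and no Hochberg adjustment. Ranges are across separate runs.

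| Test | Power |
|---|---|
| Interaction, logit | 6-7% |
| Group main effect at time zero, logit | 25-27% |
| Interaction, identity link | 66% |
| Joint group plus interaction, logit | 75% |
| Group contrast at 6 months, same logit model | 78-82% |
| Group contrast at 6 months, time as visit categories | 83% |
| Log-rank | 79-82% |

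With no true difference, the logit interaction rejected in 4.6% of runs and the log-rank test in 5.6%.

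**Sensitivity.** Assume a hazard ratio of 1.5, control mortality of 15% or 25%, and 401, 515 or 1,075 controls (674 + 401 = 1,075, both cohorts). The logit interaction has 4-9% power on cumulative status and 3-7% on deaths per interval. The identity-link interaction has 60-92%, the joint test 59-98% and log-rank 71-99%.

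**Random effect.** In a random-intercept logistic model the intercept SD ran to its cap of 15 on the logit scale. A profile likelihood on a larger simulated set kept improving up to an SD of about 20. Interaction power in two scenarios (hazard ratio 1.5) was 7% and 12%, from only 60 runs each.

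**The case against.** The strongest reply is that the article never assigns mortality to this model. Its phrase about changes over time fits functional and quality-of-life scores, the dates are collected, and a condensed article may leave outcome-specific models to a fuller plan. The same model terms also contain enough to detect the excess. A group contrast at 6 months does about as well as log-rank, and the weak main effect is weak because it is evaluated at time zero, a coding that the article does not fix.

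Part of this stands. The link and the tested coefficient are not stated, so a reader might infer too much in three ways:
- That an excess of deaths would be missed whatever is done. The identity-link, joint and 6-month results contradict this.
- That changing linear time to visit categories would not help. It does, if the visit-specific contrasts are what is reported.
- That the power figures carry over to institutionalisation. It was not simulated; only the structural argument applies, with death as a competing event.

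What does not stand is that this is mere missing detail. The article prescribes a form for all its models, lists both events among the outcomes, and exempts neither. Its stated comparison is of change, which points to the interaction, and no reading of the model uses the recorded dates.

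**Conclusion.** The point holds in a conditional form. The stated model form does not suit two of the listed outcomes. If the logit-scale interaction is the test, power against a proportional excess of deaths is about 6-7% where log-rank has about 80% (20% vs 28%, 515 vs 401). Other readings of the same model reach about 66% to about 80%. The documents do not support saying that a null mortality result is bound to follow. They do support saying that the result depends on an unstated choice, and that the wording leans towards the choice with almost no power.

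The figures rest on assumed mortality, constant hazards and unweighted, unadjusted tests. Apart from the random-intercept check, they come from a marginal rather than a multilevel model. Propensity weighting and the Hochberg adjustment would change the absolute powers. They would not create a logit slope difference that is nearly absent.

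**What to change.** State that mortality and permanent institutionalisation are exempt from the change-over-time models.

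- **Death:** analyse time to death from the recorded date, with a time origin common to the three cohorts. Use propensity-weighted Kaplan-Meier curves and a weighted Cox model with robust standard errors. Report weighted risk differences at 1, 3 and 6 months with 95% confidence intervals.
- **Permanent institutionalisation:** report weighted cumulative incidence with death as a competing event.
- **Multilevel models:** keep them for outcomes that can move both ways, such as Katz-ADL and EQ-5D.

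For the AGCH cohort this costs analysis wording only, since the dates are already collected. The open cost is confirming that both completed control cohorts hold the same dates. If they do not, use the weighted risk differences at the visits as the group comparison, in place of the interaction term.
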